## Methods and analysis

### MammoWave device and imaging algorithm

MammoWave (figure 1) is a new breast imaging device using safe, non-ionising low-power microwaves (RF signals), akin to those in mobile communications. It consists of two antennas emitting low-power (<1 mW) RF signals in the microwave band (1–9 GHz) to illuminate the breast and measure corresponding scattered electromagnetic fields (denoted as S_21_). The device’s hardware comprises a cylindrical aluminium hub internally coated with an absorption cone structure, creating an anechoic chamber to absorb reflections of electromagnetic waves that could cause noise/artefacts during data acquisition. Two motorised arms support both antennas, rotating around the azimuth to irradiate the breast and capture scattered electromagnetic fields. Both transmitting (TX) and receiving (RX) antennas are connected to a vector network analyser (VNA) for precise signal transmission and measurement. The acquisition configuration involves 10 TX positions grouped into 5 doublet sections with centres at 0°, 72°, 144°, 216° and 288°, with the RX antenna collecting signals at 80 positions around the breast for each TX position. The VNA acquires the S_21_ parameter for 1601 frequencies from 1 to 9 GHz, in 5 MHz increments. A programming logic controller inside the hub controls all components, providing shield from external interferences and structural support. The examination bed, atop the hub, includes a plexiglass cup to accommodate the volunteer’s breast without compression, with various cup sizes available for different breast sizes/types. The examination, lasting 8 min per breast, is performed with the woman lying face down.

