#### Study design

This is an open, multicentric, interventional, prospective, non-randomised clinical investigation in which 10 000 volunteers undergoing conventional breast screening examination will also undergo the MammoWave exam. Recruitment of volunteers will be performed at nine centres in different European countries: two Italian hospitals (IRCCS Policlinico San Martino, Genova; and Ospedale San Giovanni Battista—USL Umbria 2, Foligno), one Polish hospital (Pomeranian Medical University Hospital, Szczecin), two Portuguese centres (Champalimaud Foundation, Lisbon and Clínica [name] Ângelo, Lisbon), three Spanish hospitals (Hospital Universitario de Toledo, Toledo; Hospital Universitario Reina Sofía, Córdoba and Hospital General Universitario Morales Meseguer, Murcia) and one Swiss hospital (University Hospital, Zurich). The study (see figure 3) will be composed of two phases:

A preliminary phase is planned to validate and fine-tune the optimised MammoWave’s AI classification algorithm. During this phase, the initial cohort will consist of 500 women recruited from all participating clinical sites. In this preliminary stage, all asymptomatic volunteers will undergo conventional mammography and ultrasound (US) examinations at a minimum to ensure optimal diagnostic accuracy. Suspected cases will follow the standard site-specific pathways, which may include additional tests such as MRI and biopsy.During the second phase, the remaining 9500 women will be enrolled. If the MammoWave’s AI label is positive, an US examination will be conducted (in addition to conventional mammography), particularly for women with dense breasts (recall, as per the European Society of Breast Imaging (EUSOBI), recommendations for screening in dense breasts^38^), unless such examination has already been performed. Suspected cases will follow the standard site-specific pathways, which may include additional tests such as MRI and biopsy. After the enrolment of 3000 volunteers, an interim evaluation will be carried out.

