**Figure 3 F3:**
[figure not shown]
Study design and recruitment process. AI, artificial intelligence; BC, breast cancer; DBT, digital breast tomosynthesis; DM, digital mammography.

Women attending the centres for their scheduled mammogram appointment (or those who have had a mammogram within the past month) will receive information about the study and will be invited to participate on a voluntary base. Women who agree to participate, meet the inclusion and exclusion criteria and sign their informed consent document will undergo the MammoWave examination. All the eligible women will be enrolled consecutively. The reason for non-participating in the study (fear of the new exam, lack of time, lack of information, lost-to-follow-up, breasts size larger than MammoWave’s cup) will be recorded by the investigators.

On completion of MammoWave’s scan of each breast, the data will undergo processing in a cloud platform to enable real-time and high-speed data processing. The output from MammoWave will primarily consist of microwave images (along with parameters that characterise these images) and will include the label generated by the novel AI-based classification algorithm; the label will be then used for final analysis by comparing it with conventional imaging results. Thus, the microwave images (which lack detailed morphological definition) and their associated features will not serve as a basis for diagnostic decisions made by radiologists or investigators.

Regarding intervention, if MammoWave’s results (ie, labels provided by its AI classification system) indicate WSF and there is a disagreement between MammoWave output and conventional mammographic imaging, additional examinations may be warranted. These may include US, if not already conducted, particularly for dense breasts, aligning with EUSOBI recommendations due to the reduced sensitivity of conventional mammography in dense breasts.^38^ All output information, including MammoWave’s results and conventional breast examination findings, will be collected and incorporated into this study. At each site, the investigators will prospectively compare MammoWave labels with the reference standard. Furthermore, on the study’s conclusion, the MammoWave labels will undergo centralised review by blinded specialists who will not have access to the reference standard. This review aims to validate the AI-produced data.

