
#### Study outcomes

The primary outcomes will be measured as follows:

MammoWave’s sensitivity (percentage of ‘true positive’ results) while using an optimised AI-based classification algorithm.MammoWave specificity (percentage of ‘true negative’ results) while using an optimised AI-based classification algorithm.

The secondary outcomes will be measured as follows:

BC detection rates of each system by type of lesion (microcalcification, mass, asymmetry or architectural distortion group).BC detection rates, recall and positive predictive value (biopsy) of each system, also by breast density (types A and B being low-density breasts (fat), C and D high-density breasts (high content of fibroglandular tissue)).BC detection rates of each system by BI-RADS classification.^37^BC detection rates of each system by type of lesion (microcalcification, mass, asymmetry or architectural distortion group) and density (fat or high content of fibroglandular tissue).Programme screening rate, calculated as the proportion of women diagnosed with BC in the study population.BC detection rates of each system by histological type and size of the BC and BI-RADS classification.^37^MammoWave’s AI classification algorithm’s sensitivity (frequency of ‘true positive’ results) and specificity (frequency of ‘true negative’ results) after a retrospective adjustment using the data at the end of the study.BC detection rate, recalls and positive predictive value (biopsy), also by breast density (types A and B or C and D) after retrospective AI adjustment using the data at the end of the study.Programme screening rate, calculated as the proportion of women diagnosed with BC in the study population after a retrospective adjustment using the data at the end of the study.Evaluation of the reproducibility of results comparing the lectures performed at the study centres and the centralised lectures.Volunteers’ satisfaction through a properly designed questionnaire collecting women’s issues during the exam with MammoWave in the language spoken by the women.

Regarding safety outcomes, all the events will be registered, and they will be identified as related or not to MammoWave.

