The collection of AEs will start after the time that the informed consent is signed and continue until the volunteer completes the data acquisition. Investigators must obtain all information available to determine the causality and outcome of the AE and to assess whether it meets the criteria for classification as a serious AE requiring immediate notification to the Sponsor. All reported AEs will be documented on source documents and then reported on the eCRF and will include the event description, date of onset date, resolution, seriousness, severity, relatedness, cause, action taken and outcome. The investigator or an authorised designee must assess the causality, severity and relatedness for all the AEs.

Data will not be shared with any outside person or organisation and will not be used except for the development of this study.

The monitoring activities will be conducted by the CRO according to a monitoring plan agreed with the sponsor. The eCRF pages will be reviewed both on-site, by the monitor of the centre, and remotely, by the Data Management staff of the CRO. Data clarification sheets will be generated through the eCRF system, both automatically, through edit checks, and manually, by clinical research associates (CRAs) and/or data managers; the investigator will have to check and solve them. The CRAs will be permitted to inspect all study documentation provided that subject confidentiality is respected; to verify the patients’ informed consent forms, to verify the data reported in eCRF versus the source data and in case of any discrepancies, they will issue the queries. The corresponding investigator is responsible for the review and approval of all query resolutions. The CRAs will be responsible to verify the proper management of study documentation at the site.

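### Adverse event collection appears to end with the MammoWave scan, so adverse events from work-up prompted by a positive label fall outside the safety outcome

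*Protocol article*

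**What the plan says.** **The window.** Protocol article, Data collection, management and monitoring: "The collection of AEs will start after the time that the informed consent is signed and continue until the volunteer completes the data acquisition".

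**The scan.** MammoWave device and imaging algorithm describes a hub with an absorbing lining, "creating an anechoic chamber to absorb reflections of electromagnetic waves that could cause noise/artefacts during data acquisition". The same section gives the duration: "The examination, lasting 8 min per breast, is performed with the woman lying face down".

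**The label comes later.** Study design, in the text after Figure 3: "On completion of MammoWave’s scan of each breast, the data will undergo processing in a cloud platform". The label is part of the output of that processing.

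**What follows a positive label.** Study design, second phase: "If the MammoWave’s AI label is positive, an US examination will be conducted (in addition to conventional mammography), particularly for women with dense breasts", unless ultrasound has already been done. Cases judged suspected then follow each site's usual pathway, which can include MRI and biopsy. Study design also presents further examinations after a positive label that disagrees with mammography as the intervention, and the Abstract calls the labels the experimental intervention.

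**The safety outcome.** Hypothesis and objectives lists safety and tolerability of MammoWave as a secondary objective. Study outcomes says that "all the events will be registered, and they will be identified as related or not to MammoWave". Datasets places the safety analysis on all women who have the MammoWave examination.

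**The concern.** The scan uses less than 1 mW, and the article already describes the technology as harmless. Little is likely to happen during it. The device can also affect a woman through what is done because of its label, and that begins only once the scan is over. If AE collection has closed by then, a site that follows the text exactly will not record a complication of an ultrasound, MRI or biopsy that the label led to.

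At stake is the meaning of the safety result. A statement that the device is safe and well tolerated, made for a test proposed for population screening, would cover the time from consent to the end of scanning. It would say nothing about complications of the work-up that the label adds. Events not recorded when they occur are hard to recover reliably afterwards.

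**Working it through.** **Step 1: what the window covers.** The end of the window depends on the term data acquisition.

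- In MammoWave device and imaging algorithm, acquisition refers to the antenna positions, the frequencies sampled and the signals measured. Images are made after the signals have been acquired.
- In the AE sentence it is the volunteer who completes the acquisition, which fits the scan.
- One looser use exists: Study design speaks of acquired data for the whole study when it describes the later retrospective refinement of the algorithm.

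The likelier reading is therefore the end of the scan, that is 2 breasts × 8 min = 16 min of scanning, plus the time since consent.

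**Step 2: order of events.** Consent → scan → AE window closes → cloud processing → label → ultrasound if the label is positive (second phase) → MRI or biopsy if the case is judged suspected. Follow-up runs for 2 years, but the Follow-up section ties it to detection rate, recalls, positive predictive value and interval cancers, and does not mention AEs. No section extends AE collection to the work-up.

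**Step 3: what is captured anyway.** Collected variables records additional tests and biopsies with their outcomes. Study outcomes includes recalls and biopsy positive predictive value, also by density. The number of procedures will be known; AEs arising from them are not covered by the stated window.

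**Step 4: scale.** The article gives no expected number of false-positive labels. The inputs below come from Number of participants and Study design. The prevalence and sensitivity inputs reproduce the stated minimum of 8000 closely, if 10 points is taken as the half-width:

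N = 1.96² × 0.75 × 0.25 / (0.10² × 0.0092) ≈ 7,830.

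| Quantity (second phase, 9500 women) | Calculation | Result |
|---|---|---|
| Women with cancer | 9500 × 0.0092 | 87.4 |
| Women without cancer | 9500 − 87.4 | 9412.6 |
| False-positive women, 90% specificity per woman | 9412.6 × 0.10 | about 941 |
| Same, 90% per breast, breasts fully concordant | 9412.6 × 0.10 | about 941 |
| Same, 90% per breast, breasts independent | 9412.6 × (1 − 0.90²) = 9412.6 × 0.19 | about 1,788 |
| True-positive women at 75% sensitivity | 87.4 × 0.75 | about 66 |

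At 90% per woman there are about 14 false-positive women for each true positive (941 / 66). If specificity per woman were 95% or 80% (an assumed range), the false-positive count would be about 471 or 1,883. In the first phase all 500 women have ultrasound whatever the label, so label-prompted ultrasound concerns the second phase only.

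**The case against.** The strongest reply is that the stated objective concerns MammoWave itself. A window around the exposure fits that objective, and complications of a site's usual diagnostic pathway are not obviously device events. The term is also undefined and could mean the end of all study data collection. Both points have force. But the protocol itself treats the label, and the examinations after a discordant positive label, as the intervention, so leaving their complications out of the safety outcome is hard to justify. If a longer window was intended, the sentence does not tell sites so, and its end still has to be stated.

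Several stronger inferences are tempting, but the documents do not support them:

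- **That the label triggers MRI and biopsy.** It leads directly to ultrasound only, particularly in dense breasts and only if not already done. MRI and biopsy depend on the case then being judged suspected.
- **That the window contradicts the promise to register all events.** Study outcomes sets no different period; it can be read as all events within the window.
- **That an event still open at the end of the scan could not have its resolution and outcome recorded.** The sentence after the window tells investigators to obtain the available information on causality and outcome. The window limits which events enter, not how long they are followed.
- **That a biopsy complication would be coded as unrelated.** The article asks for relatedness and cause, and does not say how such an event would be coded.
- **That the false-positive burden goes unmeasured.** Specificity, recalls and biopsy positive predictive value are all outcomes.
- **That 70% specificity gives a worst case of 9412.6 × 0.30 = about 2,824 women.** Under Statistical considerations, 70% is a threshold for the lower 95% confidence limit at the interim, and falling below it leads to an update of the algorithm. It is not a specificity to apply to all 9500 women.

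**Conclusion.** The point holds in limited form. On the article's own usage, AE collection ends with the scan. AEs from the ultrasound that a positive label leads to, and from any MRI or biopsy that follows, are then outside the safety outcome, although the procedures themselves are counted.

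This rests on reading data acquisition as the scan, which is likely but not certain. The 941 to 1,788 women rest on specificity of exactly 90%, prevalence of 0.92%, and full concordance or independence between breasts for the per-breast case. For a given specificity they are an upper bound on cancer-free women exposed to extra ultrasound, because some will already have had it or would have been worked up after mammography. They do not estimate biopsies, complications or harm; the documents give no rate from which to derive those.

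The consequence is an incomplete safety outcome. The primary analysis of sensitivity and specificity is not affected. The change should be made, but it is not critical to the trial's main conclusion.

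**What to change.** In Data collection, management and monitoring, replace the open term with a stated end point: AE collection runs from consent to the end of the MammoWave scan and, for a woman whose positive label leads to additional examinations, until that work-up is complete.

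Beside the existing relatedness assessment, add an attribution category for events related to a procedure performed because of the MammoWave label. Report that category on the safety set, separately from scan-related events, so that the tolerability of the scan can still be read by itself.

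The cost is a wording change and one or two fields in the eCRF. Additional tests and biopsies are already recorded and each woman is already followed for 2 years, so no new visit schedule is implied. The downside is some extra AE reporting for label-positive women and a less favourable AE table.

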## Ethics and dissemination

This study was approved by the Research Ethics Committee of the Liguria Region (CET), Italy, on 13 November 2023 (approval number: CET—Liguria: 524/2023—DB id 13399), the Research Ethics Committee of Complejo Hospitalario de Toledo (CEIC), Spain, on 29 November 2023 (approval number: CEIC—1094), the National Ethics Committee for Clinical Research (CEIC), Portugal on 12 January 2024 (approval number: CEIC—2311KC814), the Bioethical Committee of Pomeranian Medical University in Szczecin, Poland (approval number: KB-006/23/2024) on 13 March 2024 and the Zurich Cantonal Ethics Commission, Switzerland (BASEC 2023-D0101) on 7 June 2024.

The findings of this study will be disseminated through academic and scientific conferences as well as peer-reviewed journals. Such publications will be planned and agreed on with the investigators at each site.
